## **2.Trial Purpose**

### **2.1 Primary Purpose**

To compare the effects of using only salt substitutes, only the stepwise salt supply control,

and using both intervention strategies in tandem on reducing the blood pressure of the elderly in Nursing Homes against a control group.

## 2.2 Secondary Purpose

- To investigate if salt substitutes would increase the prevalence rate of adverse reactions such as hyperkalemia, as well as whether the kidney function would affect that effect amongst the elderly in Nursing Homes by comparing the results against a control group.
- To investigate if the salt reduction strategies would decrease the development of cardiovascular diseases and the resulting deaths by comparing the results against a control group.
- To evaluate the degree of compliance and cost-effectiveness of adopting salt substitutes and the stepwise salt supply control in the elderly in Nursing Homes .
- To explore the efficacy of the intervention strategies on proteinuria in the elderly with damaged kidney function and whether the kidney function influences that effect.
- To evaluate the effect of the intervention strategies on fundus atherosclerosis.

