### **6.2 Secondary Outcome**

1. The incidence of hyperkalemia : as the main safety evaluation index. According to the 2012 Kidney Disease Improving Global Outcomes (Kidney Disease Improving Global Outcomes), serum potassium > 5.5 mmol/L is diagnosed as hyperkalemia; continuous measurement of serum potassium > 5.5 mmol/L is persistent hyperkalemia. Otherwise, it is a single attack.
2. The change in 24-hour urinary sodium、potassium and microalbumin
3. The change in diastolic blood pressure
4. European Five-Dimensional Health Scale (EQ-5D) score
5. Endpoint events (death, cardiovascular events (coronary heart disease, congestive heart failure, arrhythmia, stroke))
6. Fundus Atherosclerosis

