**Subgroup Analysis:**

Subgroup analysis will be conducted according to the baseline renal function (eGFR) stages to understand the effect modification of baseline renal function.

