### **1.2 Objectives**

The primary aim of the present study is to determine the efficacy of two practical and scalable sodium reduction intervention strategies on systolic blood pressure (SBP) among older adults living in senior residential facilities: (1) a stepwise reduction in the supply of regular salt to institutional kitchens and (2) replacing regular salt with salt substitute. The null hypothesis is that neither of the two sodium reduction interventions will reduce SBP. And if the effect of both interventions do exist, the interaction between SS and SSSC in lowering SBP during study period will be further analyzed.

The secondary aims are to:

- 1) evaluate the safety of these strategies, particularly risks of hyperkalemia with salt substitute and hyponatremia in those receiving either or both interventions.
- 2) evaluate whether sodium reduction intervention can reduce the risk of cardiovascular events and death
- 3) assess the cost-effectiveness and adherence of sodium reduction strategies
- 4) assess the impact of sodium reduction intervention on microalbuminuria

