### 5.2.1 Analysis for continuous secondary outcome

For continuous secondary outcomes we will use the same models as that for the primary outcome to test the difference between intervention groups.

If the distribution of the outcome variable is normal or mild skew, no transformation will be applied. If the outcome variable is heavily right-skewed, a log transformation will be conducted.

If the outcome variable is heavily left-skewed, a power transformation (e.g. box-cox transformation) will be conducted.

Results for continuous secondary outcomes will be reported in **Table 2** and **Table 3**.

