#### 5.6 Subgroup analysis

The following pre-specified subgroup analyses will be performed on the primary outcomes and safety outcomes stratified by:

- 1) baseline blood pressure:
  - a. normal: baseline SBP < 140mmHg and DBP < 90mmHg
  - b. stage 1: baseline BP 140-159/90-99mmHg
  - c. stage 2 or above: baseline SBP > 160mmHg or DBP > 100mmHg
- 2) hypertension status:
  - a. normotensive: baseline BP < 140/90mmHg and not taking antihypertensive medication within 2 weeks before baseline
  - b. hypertensive: had baseline SBP  $\geq$  140mm Hg or DBP  $\geq$  90mmHg, or on antihypertensive medications within 2 weeks before baseline
- 3) region:
  - a. Changzhi
  - b. Xi'an
  - c. Hohhot
  - d. Yangcheng
- 4) Sex:
  - a. Male
  - b. Female
- 5) Age
  - a. < 70 years
  - b.  $\geq$  70 years

Using 70 years as the cut-off is because the mean age at the baseline was about 71 years.
- 6) educational attainment
  - a. illiterate, semi-illiterate or completed primary school
  - b. completed junior high school or above

Results will be presented on forest plots in **Figure 3** with the interaction results alongside

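### The SAP drops, without saying so, the protocol's exploratory objective on proteinuria in residents with damaged kidney function and the planned subgroup analysis by eGFR stage

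*Supplement*

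**What the plan says.** **Protocol V1.4**
- Section 2.2 lists among the secondary purposes: "To explore the efficacy of the intervention strategies on proteinuria in the elderly with damaged kidney function", and adds the question whether that effect depends on kidney function. It does not define damaged kidney function.
- Section 6.2 supplies the outcome that carries this aim: "The change in 24-hour urinary sodium、potassium and microalbumin".
- Section 9, under the subgroup heading: "Subgroup analysis will be conducted according to the baseline renal function (eGFR) stages to understand the effect modification of baseline renal function". It names no outcome, cut-off or model.

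**SAP**
- Section 1.2, secondary aim 4: "assess the impact of sodium reduction intervention on microalbuminuria". Neither the target group nor the question about kidney function appears.
- Section 5.2 classes 24-hour microalbumin as an effectiveness outcome, and 5.2.1 says: "For continuous secondary outcomes we will use the same models as that for the primary outcome to test the difference between intervention groups".
- Section 5.6: "The following pre-specified subgroup analyses will be performed on the primary outcomes and safety outcomes stratified by" six factors, namely baseline blood pressure, hypertension status, region, sex, age and education. Figure 3 adds antihypertensive medication. None is renal.
- Section 5.9, which tabulates departures from the protocol, covers the primary outcome and its model, the continuous secondary outcomes, and the added renal dysfunction outcome. It mentions neither the proteinuria objective nor the eGFR subgroup.

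**The concern.** The protocol puts a question about a particular group of residents and about effect modification. The SAP answers a different one, the average effect on microalbumin across everyone. A null pooled result could then be read as showing no effect on proteinuria, although the group named in the objective was never examined. Any renal-subgroup result reported later would be post hoc, because the governing analysis plan does not specify it.

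**Working it through.** The point rests on no figure in the plan, so the check is mainly one of text, followed by two illustrations.

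**1. Can any SAP analysis deliver the objective?**
- *Main model (5.1.1, applied to microalbumin by 5.2.1).* Its terms are intervention, baseline value of the outcome, time, and random effects for individual and facility. It has no restriction on eGFR and no intervention-by-eGFR term.
- *Adjusted model (5.1.2.1).* It adds covariates that differ at baseline with p<0.05. If eGFR entered this way, it would enter as a main effect, which does not estimate effect modification.
- *Subgroups (5.6).* Microalbumin is neither the primary outcome nor in the safety list of 5.3.1, so it gets no subgroup analysis. Adding eGFR as a factor would not change that unless the scope of outcomes were widened too.
- *Other uses of eGFR <60.* It defines the incident renal dysfunction outcome (2.3, item 6) and is one of several adjustment conditions in the safety incidence models (5.3.2.1). Neither concerns microalbumin.

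So no analysis in the SAP addresses either half of the objective.

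**2. What could pooling hide?**
Let p be the share of residents with damaged kidney function, and r the effect in the others as a fraction of the effect in that group. On the analysed scale:

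pooled effect / target-group effect = p + (1 − p)r

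Neither p nor r is in the documents. Assuming p = 0.20:
- r = 1: 0.20 + 0.80 × 1 = 1.00, so nothing is lost.
- r = 0.5: 0.20 + 0.80 × 0.5 = 0.60.
- r = 0: 0.20, the extreme case.

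At r = 0 the ratio is simply p, so an assumed range of 10% to 40% gives 0.10 to 0.40.

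**3. How precise would an analysis of the target group be?**
Inputs from protocol section 10 and SAP 2.5: 48 facilities, 16 evaluable in each (48 × 16 = 768), ICC 0.02. The ICC is stated for SBP and is borrowed here. Each strategy is compared 24 v 24 facilities. With m = 16p evaluable per facility, design effect 1 + (m − 1) × 0.02, and effective n per side = 24m / design effect, the effect detectable with 80% power at two-sided 0.05 is (1.96 + 0.84) × √(2/n) in SD units.

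| Assumed p | Evaluable residents | Detectable effect (SD) |
|---|---|---|
| 10% | 77 | 0.64 |
| 20% | 154 | 0.46 |
| 30% | 230 | 0.38 |
| 40% | 307 | 0.34 |
| All residents | 768 | 0.23 |

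For p = 20%: m = 3.2, design effect 1.044, n = 76.8/1.044 = 73.6, and 2.80 × √(2/73.6) = 0.46.

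**The case against.** The strongest reply is that the protocol does plan for this. Its section 9 subgroup by eGFR stage is not tied to any outcome, and the same section lists urinary microalbumin among the secondary outcomes. Read together, they cover in outline whether kidney function alters the effect, and eGFR stages would isolate residents with low eGFR. This stands as far as it goes. A reader might infer that the objective has no analysis anywhere in the plan, and the documents do not support that. The gap is in the SAP. Even so, the protocol paragraph names no outcome, and it could equally serve the separate protocol aim on hyperkalemia and kidney function, so it does not by itself specify the proteinuria analysis. The SAP then leaves it out.

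A reader might also infer that any effect in the target group is bound to be diluted, and put a size on it. For example, a 20% reduction in geometric mean confined to 15%, 20% or 30% of residents would pool to 1 − exp(p × ln 0.8) = 3.3%, 4.4% or 6.5%. That needs an effect of exactly zero in everyone else, an assumed share, and analysis on the log scale. SAP 5.2.1 takes logs only for heavy right skew, and its Table 2 shell reports microalbumin in mg/d. The protocol itself treats effect modification as an open question. Dilution is therefore a possibility, with no size that the documents support.

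Two further objections stand. The aim is worded as exploratory and is one of five secondary purposes. And eGFR <60 is not a subgroup definition already adopted for this purpose; it selects on filtration, not on albumin excretion.

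**Conclusion.** The point holds as a mismatch between protocol and SAP. The SAP narrows the proteinuria aim to all residents, omits the protocol's eGFR-stage subgroup, and records neither change in 5.9. The loss that needs no assumption is that neither the effect in residents with damaged kidney function nor its modification by kidney function will be estimated. Understatement by the pooled estimate is conditional on a larger effect at reduced eGFR. Severity is minor, since a stated but exploratory secondary aim is affected and the SBP conclusion is not.

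**What to change.** In SAP 5.2.1 and 5.6, pre-specify as exploratory the effect of SS and of SSSC on month-24 24-hour microalbumin by baseline eGFR category. State the categories: either the eGFR stages that protocol section 9 refers to, or <60 v ≥60 mL/min/1.73m². Adjust for baseline microalbumin, with facility as a random effect, and fit the treatment-by-baseline-eGFR interaction in all residents. Report the result beside the pooled estimate. Otherwise, state in 5.9 that the objective and the eGFR subgroup are dropped, with the reason.

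The cost is SAP wording and one extra model per strategy, or one row in 5.9. No new data are needed: serum creatinine is measured at baseline, eGFR is already in the baseline table shell, and 24-hour urine is scheduled at baseline and month 24. The downside is imprecision, as the table of detectable effects shows, so the result must be labelled exploratory and a null finding in the subgroup must not be read as absence of effect.

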## 3.Trial Design

This is a multi-center, is a 2-year  $2 \times 2$  factorial, cluster-randomized controlled trial. Senior residential facilities (geracomiums/old folk's homes) are randomized and used to test two salt reduction strategies, namely, 1) introduction of low-sodium salt substitute (SS) compared to continued use of regular salt.; and 2) Manage and control the salt procurement and supply channels of institutional kitchens ,which will be achieved together with health education and health promotion for chefs. This will be referred to as the "stepwise salt supply control"

48 eligible senior residential facilities in Changzhi, Xi'an, Hohhot, and Yangcheng will be selected and assigned into one of the following four intervention groups using stratified randomization: 1) SS + SSSC; 2) SS only; 3) SSSC only; and 4) No SS and no SSSC (control). The intervention will be last for 2 years. Follow-ups will be conducted at 6, 12, 18, and 24 months after the intervention.

[figure not shown]

## 4. Participants

### 4.1 Inclusion and Exclusion Criteria of Nursing Homes

Inclusion Criteria:

- 1) Have more than 20 elderly people staying there for a prolonged period.
- 2) Have a record of the elderly's entry and exit from the nursing home, where they went, the reason they left, and the duration they left for.
- 3) Have a person responsible for the purchase of food and condiments, as well as an area

designated for the storage and safekeeping of food.

4) Responsible for preparing the food consumed by the elderly and must not purchase processed food from outside the nursing home more than once a week.

5) Must be willing to accept the intervention to reduce salt usage and have a high degree of cooperation.

6) Signed the partnership agreement.

Exclusion Criteria:

1) Have participated in any salt reduction or other intervention trials in the past or currently.

## **5. Trial process and data collection**

### **5.1 Preparation Period**

Relevant organizations in the various regions will be responsible for the selection of eligible nursing homes in their region based on the inclusion criteria. After the nursing homes confirm their participation and sign the partnership agreement, the relevant organizations will head down to the nursing homes and select eligible elderly based on the inclusion and exclusion criteria.

### **5.2 Baseline Assessments**

Baseline assessments will be arranged and conducted after the signing of the partnership agreement and informed consent forms.

**Investigations on the nursing homes include:**

- Accommodation cost of the elderly
- Types, quantity, and frequency of condiments purchased as well as the frequency and quantity of processed food and foods with high salt content purchased
- Usage of the salt and condiments purchased: Cooking, homemade preserved vegetables or fermented vegetables, feeding livestock

**Investigations on the elderly include:**

-Contents:

**Questionnaire: General Demographic Data:** Gender, age, ethnic group, education level, marital status, and medical insurance of the participant.

**Lifestyle Information:** Smoking, alcohol consumption, level of physical exercise, frequency of fruit and vegetable consumption.

**Level of Satisfaction in Meals:** How much they liked the meals provided by the nursing home, self-assessment of the level of saltiness in meals.

**Disease History:** Whether or not they are suffering from hypertension, diabetes, stroke, coronary heart disease, kidney disease, cancer, or COPD. As well as other disease histories and whether they are receiving treatment.

**Information on Antihypertensive Drugs:** Type, specification, and frequency of consumption of antihypertensive drugs.

**Occurrence of an Endpoint Event:** Whether or not there is all-cause mortality or cardiovascular events (coronary heart disease, congestive heart failure, heart arrhythmia, and stroke).

**Health Status:** Will be evaluated using the EuroQol Five Dimensions Questionnaire (EQ-5D).

**Physical Examination:** Weight, height, blood pressure, heart rate.

**Laboratory Examination:** Serum electrolytes (blood potassium), blood sugar and four items of blood lipid, kidney function (serum creatinine), and blood routine. Levels of 24-hr urinary sodium, urinary potassium, urinary creatinine, and quantitative microalbuminuria.

**Eye Fundus Examination:** Vision test and funduscopy.

**-Methods:**

- Questionnaire and Health Status: Professional investigators who have undergone standardized training will read through and check the nursing homes' travel records and medication information. The participants will be asked for the rest of the information. The information will be further verified through the New Rural Co-operative Medical System.
- Physical Examination: Professional investigators who have undergone standardized training will conduct the physical examination on the participants. See Annex 4 for specific details on the examination methods.
- Laboratory Examination: Participants will be required to empty their bladder and record the time in the morning. They will then be given a 24-hr urine bucket and urine cup to collect their urine over the next 24 hours. The urine collection will be stopped at the same time on the morning of the second day. The urine volume of the participants over 24 hours, left out situations of urine, and the start and end time of the collection will be recorded. After mixing the 24-hr urine sample thoroughly, 5ml of urine will be collected and stored at -20°C. 6.5ml of venous blood will be collected from participants on an empty stomach on the morning of their physical examinations. See Annex 5 for the specific requirements on blood sample collection, packaging, transportation, storage, and determination.
- Eye Fundus Examination: A Chinese standard long-distance visual chart will first be used to investigate the normal vision of the participants. Participants who are wearing glasses during the examination will be tested for their vision with glasses; participants who are not wearing glasses during the examination will be tested for their naked vision. Photographs of the participants' eye fundus were then taken using fundus cameras (TRC-NW Series (Topcon), CR-2 AF Model (Canon), etc.) in non-mydratic conditions.

### **5.3 Randomization**

The randomization process of this research will be conducted by the Peking University Clinical Research Institute. An independent statistician carried out the randomization after the baseline characteristics had been collected for study sites and individual participants. Nursing homes are

stratified by region before being randomly assigned to the experimental groups.

## **5.4 Intervention Scheme**

### **Intervention Strategies**

There are two main intervention strategies, namely salt substitute and stepwise salt supply control. All nursing homes will also receive general health education on how salt reduction can prevent hypertension and cardiovascular diseases.

#### **1. General Health Education on Salt Reduction**

This research will provide a general health education activity to all participating nursing homes (including nursing homes in the control group). The specific details are as follows:

Managers of all the nursing homes will be invited to the trial initiation meeting held at the the study center of the various regions. The aim, design, and requirements of the trial will be explained to them. This includes the health benefits and the existing conflicts that the international research community has on salt reduction and cardiovascular diseases.

At each facility, health education program on salt reduction will be delivered on the baseline survey initiating meeting (with the managers of nursing home, cooks, and all elderly living in the nursing home participated). Posters will also be put up. The main contents of the education program are: Basic health information (The dangers of consuming too much salt, the recommended amount of salt intake in China, and how to reduce salt intake, etc.).

#### **2. Replacing Regular salt with a Salt Substitute**

##### **2.1 Salt Substitute management (supply and distribution)**

Nursing homes that are allocated to the salt substitute group will use a standardized salt substitute product as assigned by our study. They will do a 100% replacement of the regular salt that they were using. This will be managed and implemented by an assigned professional from the site. Any personnel who are not involved in the trial cannot come into contact with the salt substitute used in this trial. The salt substitute to be used in this trial is a standardized low-sodium salt that contains potassium which can be found on the market. It will be tested by an independent third party to ensure that the product is qualified.

The salt substitute used in the trial must be supplied to the specific nursing homes in strict accordance to the trial requirements. The purchaser and cook of the nursing homes must not hand over or sell the salt substitute. They must not use the salt substitute for something else and most importantly, they must not let non-participants of this research consume the salt substitute.

The trained local investigators will audit the salt supply records once every three months to ensure that the nursing homes are using the salt substitute, so as to evaluate the compliance of the intervention.

## **2.2 Training on the Correct Usage of the Salt Substitute**

This research will provide extra training on the correct usage of the salt substitute for the nursing homes in the SS group. The purchasers and managers of salt in these nursing homes will receive a standardized training and learn about the composition of the salt substitute, its effects, and potential side effects. The core pieces of information are "the salt substitute is not less salty but can lower blood pressure" and "the salt substitute is still a salt, so it's best to still cut down on it".

## **3. Kitchen-based SSSC program**

### **3.1 Controlling Salt Supply with the Aim of Gradually Reducing Salt Usage in the Kitchens**

Assigned personnel from the local study center will be responsible for the target setting and implementation of the salt supply control. This person and the person responsible for the salt substitute intervention strategy cannot be the same person.

#### **➤ Management Target and Plan for Gradual Reduction of Cooking Salt Usage**

The main strategy behind this intervention is to control the person purchasing salt for the nursing homes, so as to gradually reduce salt usage in the kitchen in a stepwise manner. The intervention strategy consists of 4 stages. The first stage is the preparatory stage, which lasts for a month. The nursing homes will continue the amount of salt they normally use in their cooking and begin recording how much salt they use to be used as a baseline reference. The second stage consists of two steps, with every step lasting 3 months for a total of 6 months. At this stage, the salt reduction target for every step will be 10% from the nursing home's baseline salt usage. The third stage consists of four steps, with every step lasting 3 months for a total of 12 months. At this

stage, the salt reduction target for every step will be 5% from the nursing home's baseline salt usage. The fourth stage is the maintenance stage. The amount of salt used in the nursing homes should now decrease to 60% of their baseline salt usage. This will not be lowered further until the end of the research. (As per diagram below)

[figure not shown]

➤ Management of Stepwise Salt Supply Control and evaluation

Nursing homes that have been assigned to the SSSC group will send their purchasers and cooks to receive standardized technical training. See Annex 2 (Stepwise Salt Supply Control Technical Training) for detailed contents of the training.

Through the training, purchasers will learn and understand the salt reduction targets throughout the various stages and the specific ways to control salt supply; and cooks will learn how to weigh 5% and 10% of their ordinary salt usage. The two parties have to learn the reason for salt reduction and techniques to communicate with the elderly.

The person-in-charge from the sub-sites will audit the stock in and stock out records once every three months to evaluate if the goal for the stage has been met. This will be the basis for the

decision on whether to activate the next stage of the intervention and intervention target. Nursing homes are considered to have met the target if the difference between their actual salt usage and the target salt usage is no more than  $\pm 30\%$  and can move on to the next stage. A forum will also be held for the elderly to gather feedback and opinions. For nursing homes that fail to meet the target, a forum has to be held between the managers of the nursing homes, personnel controlling the supply of salt, cooks, and an elderly representative to identify challenges and resolve them. These nursing homes will also keep their original salt reduction target for the next 3 months. They will only go on to the next target after they meet their current target. Should a nursing home fail to meet half of the expected target for 2 consecutive stages, the intervention strategy will end for the nursing home at their current salt usage level. Should a nursing home exceed the salt reduction target of their current stage, they will be requested to slow down their rate of salt reduction and comply with the planned target.

➤ Incentives

Results-based incentives for the purchasers and cooks will be set up in accordance with the salt reduction effects and progress of the nursing homes.

